### Data Collection

Data collection takes place at baseline, when the child is 4-6 months of age, prior to commencing CF (CF1), and then around 8 months of age (CF2) and around 10 months of age (CF4) post randomization. Prior to the baseline clinic visit, written informed consent is obtained, and parents are given verbal and written information about participation. Questionnaires collecting information on sociodemographic characteristics and participating infant health are completed digitally using REDCap electronic data capture tools hosted by the University of Auckland [20]. At baseline, participants are assessed according to the schedule presented in Table 1 and either provided with a 2-month supply of kūmara powder or the equivalent value in gift vouchers (if randomized to the C group).

**Table 1 table1:** SUN^a^ trial schedule of enrolment, interventions, and assessments.

Timepoint			Study period											
			Enrollment		Allocation		Post allocation							Closeout
							Baseline		CF2		CF4			
Infant age			<4 mo		4-6 mo		≥4-6 mo		≤8 mo		≤10 mo		>10 mo	

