### Dietary Intake and Feeding Behaviors

Infant dietary intake is assessed using a 3-day food record at CF2 (infant approximately 8 months of age) and CF4 (infant approximately 10 months of age). Parents are asked to record the participating infant’s food and drink intake over 3 consecutive days, with even distribution across weekdays and weekends at a group level. Parents are instructed on how to complete the 3-day food records and use household measures to describe their infant’s dietary intake. Diet records will be analyzed with FoodWorks (version 10; Xyris Software) using the New Zealand Food Composition database FOODfiles 2018 (version 01).

At baseline (CF1), infant feeding practices such as method (breastfeeding, formula, or mixed feeding) and frequency or amount are recorded. A questionnaire at baseline and diet records at CF2 and CF4 captures the volume of milk intake (expressed breast milk or formula). Breast milk remains an important component of the diet and has important impacts on both the gut microbiota and immune function. Breast milk volume will be estimated using the previously validated methodology, whereby breastfeeding is recorded as time (minutes) and quantity estimated using a conversion factor of 10 mL/min, with a maximum of 10 minutes of breastfeeding or 100 mL of breast milk [34,35].

Habitual maternal food and nutrient intake will be assessed using a semiquantitative food frequency questionnaire, which has previously been validated in the New Zealand setting [36].

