Logistic regression models will be used to test the difference in the proportion of participants with at least 1 episode of RTI at a 4-month follow-up between the K+ and C groups (primary comparison), adjusted for gender (stratification factor). The effect of the intervention will be estimated between the 2 groups using a model-adjusted odds ratio with a 95% CI. Statistical tests will be 2-sided at a 5% significance level.

Generalized linear regression models will be used on other secondary outcomes to test the group differences at 2- and 4-month follow-ups separately, using a link function appropriate to the distribution of the outcome measure. All regression analyses will be adjusted for baseline outcome value (if available) and gender. The effect of the intervention will be estimated and tested using a model-adjusted point estimate on the group difference with a 95% CI and a 2-sided *P* value. Multiple testing on secondary outcomes will not be adjusted as they are considered exploratory and provide supporting information on the primary outcome. A random-effects mixed model will be used on the outcomes collected repeatedly over time to account for correlated data collected from the same participants and take into account any missing data in maximum likelihood estimates. The consistency of the short- and long-term effects of the dietary intervention will be assessed using the interaction term between the treatment group and visit. The effects of the intervention on predefined subgroups will also be assessed, and separate subgroup analyses will be considered if a sufficient number of participants are recruited.

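### The covariate list for the secondary models leaves out baseline milk-feeding method, which is already recorded: a modest loss of precision, not a bias

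*Protocol article*

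**What the plan says.** The Statistical Analysis section of the protocol article gives the secondary models in one paragraph. "Generalized linear regression models will be used on other secondary outcomes to test the group differences at 2- and 4-month follow-ups separately", with a link function chosen to suit each outcome. The covariates follow: "All regression analyses will be adjusted for baseline outcome value (if available) and gender". For repeated outcomes, "A random-effects mixed model will be used on the outcomes collected repeatedly over time", and no further covariates are named. The status of these outcomes is also stated: "Multiple testing on secondary outcomes will not be adjusted as they are considered exploratory".

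Under Dietary Intake and Feeding Behaviors, the article reports that "At baseline (CF1), infant feeding practices such as method (breastfeeding, formula, or mixed feeding) and frequency or amount are recorded". The same paragraph explains why milk feeding matters: "Breast milk remains an important component of the diet and has important impacts on both the gut microbiota and immune function".

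Three other places point the same way:
- The Background describes a distinct microbiota in breastfed infants and says that continued breastfeeding during complementary feeding can alter microbial patterns. It also reports observational evidence linking breastfeeding to fewer and less severe respiratory infections.
- The section on measuring breast milk refers to a continuing effect of breast milk on infant gut microbiota during complementary feeding.
- The Randomization section stratifies by gender only.

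**The concern.** The article leaves out of its secondary models a variable that it treats as a driver of the outcomes being modelled and that it already collects. The covariate sentence covers all regression analyses, so this is a stated choice and not a detail left open.

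The baseline outcome value need not make feeding method redundant. The baseline fecal sample is taken before solids, and the Background says the taxa and short-chain fatty acids of interest rise once solids begin. The pre-solids value may therefore predict the 4-month value only in part. Feeding method at baseline should help to predict whether breastfeeding continues, which the article says affects later change.

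For illness frequency, medication and antibiotic use, the outcome is built from daily records kept during the trial and appears to have no true pre-randomization counterpart. Those models may then adjust for gender alone.

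At stake is the precision of the K+ versus C and K versus C comparisons on the microbiome, which is part of the stated objective, and on the metabolite, immune and illness outcomes.

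**Working it through.** **The plan's own figure.** The Sample Size section concerns the primary outcome. A 20-point absolute difference that is also a 25% relative reduction implies 0.20/0.25 = 80% in C and 60% in K+. At 80% power and two-sided 5%, the pooled formula gives 82 per arm and the unpooled formula 78.5, so 79. Power at 80 per arm is 79.4%. Allowing for 20% loss, 80/0.80 = 100 per arm, or 300 in total. The figure reproduces. It is used here only for the 80 evaluable infants per arm.

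**Benchmark for a continuous secondary outcome.** In units of the residual SD under the current covariate list, the difference detectable with 80% power is (1.96 + 0.84) × √(2/80) = 0.44 SD.

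**Effect of adding a covariate.** Let R² be the share of that residual variance that feeding method explains. The documents do not give it, so it is assumed. The interval width is multiplied by √(1 − R²), the equivalent sample size is 80/(1 − R²), and power is evaluated at the 0.44 SD difference.

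| Assumed R² | CI width ratio | Equivalent n per arm | Power |
|---|---|---|---|
| 0 | 1.000 | 80.0 | 80.0% |
| 0.02 | 0.990 | 81.6 | 80.8% |
| 0.05 | 0.975 | 84.2 | 82.0% |
| 0.10 | 0.949 | 88.9 | 84.0% |
| 0.20 | 0.894 | 100.0 | 87.9% |

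**What these R² values mean.** With feeding reduced to two groups, a share p breastfed and a remaining difference of d residual SDs, R² = p(1 − p)d².
- At p = 0.5, R² = 0.02 needs d = √(0.02/0.25) = 0.28, and R² = 0.20 needs d = √(0.20/0.25) = 0.89.
- At p = 0.8, the same two values need d = √(0.02/0.16) = 0.35 and d = √(0.20/0.16) = 1.12.

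The upper end of the range therefore needs a large difference left over after adjustment for the baseline value.

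**Simulation check.** There were 5,000 trials per setting, 80 per arm, and an assumed baseline-to-outcome correlation of 0.5. The extended list added a two-level feeding variable and a continuous age variable that shared the R² equally; the formula depends only on the total. Power under the current and extended lists was:
- R² = 0: 79.2% and 78.8%
- R² = 0.02: 79.3% and 79.7%
- R² = 0.05: 78.2% and 80.0%
- R² = 0.10: 78.8% and 82.2%
- R² = 0.20: 78.8% and 86.9%

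Type I error was 4.5% to 5.7%, and the estimates were unbiased under both lists.

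**Chance imbalance.** With 80 per arm, the 95% range of imbalance in a feeding category is 1.96 × √(2p(1 − p)/80). That is about ±12 points at a prevalence of 20% and ±16 points at 50%. The variance this adds to the estimated difference is d² × 2p(1 − p)/80. Divided by the total variance 2/80, it equals p(1 − p)d², which is the same R² as above. It is therefore not a second harm on top of the lost precision.

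**The case against.** The strongest reply is that nothing here is wrong. Baseline value plus the stratification factor is a standard prespecified model, the outcomes are labelled exploratory, and a separate analysis plan may add outcome-specific covariates. The first two points stand and limit the weight of the finding. The third is weakened because the sentence is written to cover all regression analyses.

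A second reply is that the baseline value already carries part of the feeding signal, and that the article attributes later change to continued breastfeeding, for which baseline method is only a proxy. This also stands. The gain may be near zero for some outcomes, which is why R² is shown as a range.

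A reader might go further and infer several things that the documents do not support:
- **Bias or confounding by feeding method.** Randomization balances feeding method in expectation, and the ordinary standard error already covers chance imbalance, so interval coverage is kept.
- **The same loss for sleep.** No section calls feeding method or age prognostic for sleep.
- **A material loss from omitting age.** The article says "Data collection takes place at baseline, when the child is 4-6 months of age", but nowhere that these outcomes change quickly across that span. It ties change to solids, which no infant has started at baseline. The abstract describes 6-month-old infants, so the real spread may be narrower. Exact age is implied by screening but is not named as an analysis variable.
- **A fault in the primary RTI model.** That model is specified separately, and this point does not concern it.

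**Conclusion.** The point holds as a modest improvement in efficiency. It centres on baseline feeding method in the secondary microbiome, metabolite, immune and illness models. For continuous outcomes with 80 per arm, the interval would narrow by about 1% to 11% and power would rise from 80% to about 81% to 88%.

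This rests on an assumed partial R² of 0.02 to 0.20 and on a linear model. At R² = 0 the simulated cost was 0.4 percentage points of power. Where no baseline value exists the gain is likely larger, but the documents give no figure from which to size it. Blood sampling is optional, so the immune analyses may have fewer than 80 per arm.

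The current analyses would be valid if left as they are.

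**What to change.** Before unblinding, amend the covariate sentence so that the secondary microbiome, metabolite, immune and illness models adjust for:
- the baseline outcome value, where there is one;
- gender;
- milk-feeding method at baseline (breast, formula or mixed).

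State in advance how sparse feeding categories will be combined, above all for the optional blood outcomes. Use the baseline record only. Milk intake at CF2 and CF4 is measured after randomization and should not enter these models as a covariate. Keep the current model as a sensitivity analysis. Baseline age may be added but is optional. If the sponsor prefers the present list, a sentence justifying the omission would do.

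The cost is one sentence and about 2 degrees of freedom, with no new data. Under non-linear links such as the logit, the adjusted estimate becomes conditional on feeding method, so the gain is not simply a narrower interval around the same quantity. The report should say so.

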The aim of the SUN (seeding through feeding) randomized controlled trial is to evaluate the effect of consuming kūmara (sweet potato) (K) or kūmara with added banana powder containing resistant starch (RS; K+) compared to the C at 4 months post randomization on the prevalence of RTI and the development of the gut microbiome. We will also explore how changes in the gut microbiome influence immune development. Kūmara (sweet potato) is commonly used in CF and is a source of starch and nondigestible carbohydrates. RS is a carbohydrate that resists digestion and acts as a prebiotic food for beneficial gut bacteria.

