### Secondary Outcomes

Secondary outcomes include the following: (1) between-group differences in other measures, including infant health, assessed using daily records of illness (reporting frequency, illness type, medication prescribed, use of antibiotics, and antibiotic course length). Differences in infant fecal microbiome relative abundance and diversity; (2) differences in infant fecal concentrations of SCFAs and intermediate metabolites; (3) differences in immune cell development, as determined by high-dimensional flow cytometry, as well as the magnitude of antibody responses to the oral rotavirus vaccine in infants paired with rotavirus-specific secretory immunoglobulin A (IgA) quantification in breast milk (breastfeeding mothers only); and (4) differences in nighttime sleep, daytime sleep, and activity of infants assessed using actigraphy and sleep dairy.

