### Sample Size

A sample size of 80 participants per group will have 80% power at the 5% significance level (2-sided) to detect an absolute difference of 20% between the K+ and C groups on the primary outcome. This is equivalent to a 25% relative reduction, assuming a retention rate of 80%. To allow for a 20% loss to follow-up, we aim to recruit 300 participants in total (n=100 per group; Figure 1).

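### The stated rule of no multiplicity adjustment covers the high-dimensional microbiome, metabolite and immune-cell families, where false-discovery control is needed; no lead model is named where two overlap

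*Protocol article*

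**What the plan says.** The Statistical Analysis section reserves the confirmatory test for one comparison, K+ versus C on respiratory tract infection (RTI). The other group comparisons are secondary. On the remaining outcomes it says: "Multiple testing on secondary outcomes will not be adjusted as they are considered exploratory and provide supporting information on the primary outcome".

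Each secondary outcome still gets an estimated group difference, a 95% CI and a two-sided P value. Generalized linear models are to be used "to test the group differences at 2- and 4-month follow-ups separately". The same paragraph adds: "A random-effects mixed model will be used on the outcomes collected repeatedly over time". It does not say which result leads when an outcome falls under both.

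The Secondary Outcomes section includes "Differences in infant fecal microbiome relative abundance and diversity", fecal short-chain fatty acids and intermediate metabolites, and immune cell development by high-dimensional flow cytometry. The fecal methods section adds shotgun and 16S sequencing and a mass-spectrometry metabolome.

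The Background section aims to evaluate the foods' effect "on the prevalence of RTI and the development of the gut microbiome". The Abstract's Objective says the same, and its Conclusions section expects to learn how the food affects the relative abundances of microbial species.

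**The concern.** Leaving exploratory outcomes unadjusted is reasonable for a short list of named measures. It works less well for a family with tens or hundreds of features, because a share of the null features will cross 5% by chance and a reader cannot tell these from real effects.

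The reason given for not adjusting is that the outcomes support the primary outcome. That fits poorly with an objective that names the microbiome beside RTI. Statements about particular taxa, metabolites or cell subsets could then rest on unadjusted P values.

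This cannot simply be left to a statistical analysis plan that is not shown. The article states a rule, and a plan that applied false-discovery control would contradict it.

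The overlap of models raises a smaller question. For an outcome measured at 2 and 4 months, the per-visit regression and the mixed model can each give a result for the same contrast, and nothing fixes in advance which one is reported.

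**Working it through.** **The plan's own figure.** The only error rates and power stated concern the primary comparison: 80 per group "will have 80% power at the 5% significance level (2-sided) to detect an absolute difference of 20% between the K+ and C groups". An absolute difference of 20 points that is also a 25% relative reduction implies 0.20 / 0.25 = 80% in C and 60% in K+. The usual two-proportion formula for 80% versus 60% gives 82 per group (79 with unpooled variance). Power with 80 per group is 79.4%, and 80 / 0.80 = 100 to recruit. The stated figure is reproduced, and the present point does not touch it.

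**Inputs for the secondary outcomes**
- Level: 5%, two-sided (Statistical Analysis).
- Contrasts: up to 3 among the three arms (Statistical Analysis).
- Follow-up visits: for feces, 2 according to Table 1 and the fecal methods section, although the Abstract lists only baseline and 4 months. For blood, 1 (baseline and 10 months only, and optional).
- Features per family, m: not stated. Assumed 100, range 50 to 300.

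**Expected false positives.** If all m features are null and tested singly, the expected number is 0.05 × m per contrast and visit, whatever the correlation.
- m = 50: 2.5
- m = 100: 5
- m = 300: 15

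Per 100 features over all three contrasts, this is 5 × 3 × 2 = 30 for feces if both visits are analyzed, and 5 × 3 × 1 = 15 for blood.

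**Chance of at least one false positive.** Under independence it is 1 − 0.95^m. Under correlation it was simulated with equicorrelated normal test statistics (20,000 replicates).

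| m | Independent | Correlation 0.5 | Correlation 0.8 |
|---|---|---|---|
| 50 | 92% | 63% | 30% |
| 100 | 99.4% | 78% | 36% |
| 200 | >99.9% | 90% | 42% |

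**If only summary measures are tested.** The Secondary Outcomes section names roughly 15 measures. One test of each gives 1 − 0.95^15 = 54% under independence, with 0.05 × 15 = 0.75 false positives expected.

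**Two models for one contrast.** Testing one null hypothesis with two statistics and counting either as a hit raises the error from 5% to about 6.5% if they correlate at 0.95, and to about 7.1% at 0.90. This inflation is small. The estimates can still differ: a per-visit regression uses only infants observed at that visit, the mixed model handles missing data through the likelihood, and the Sample Size section plans for 20% loss.

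**The case against.** The strongest reply is that the choice is disclosed and conventional. The article calls these outcomes exploratory, protects the confirmatory error with a single comparison, and says in the Discussion that the study is powered for RTI while the design allows the microbiome to be explored. All of this stands. It means that the primary conclusion is safe and that the rule is acceptable for short outcomes such as illness, antibiotic use and sleep.

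A second reply is that the article never says each taxon, metabolite or cell subset is tested singly, and that it gives no feature count. That also stands, so the figures above are conditional. The rule as worded nevertheless admits no exception for these families, and the Abstract's Conclusions section speaks of abundances at species level.

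Three stronger readings are tempting but not supported:
- **False signals are near certain.** This needs many features tested singly and close to independent. With strong correlation, the chance of any false positive among 100 tests falls to between 36% and 78%.
- **The two models materially inflate error.** They add about 1.5 to 2.1 percentage points. They also have partly different tasks, since the mixed model addresses missing data and the group-by-visit interaction.
- **Abundances will be analyzed by ordinary regression that ignores their constraint.** The article specifies generalized linear models with a link suited to each outcome. The scale for compositional data, and the choice of a single diversity index, are matters for a fuller plan or of preference.

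**Conclusion.** The point holds in limited form. A stated rule excludes multiplicity adjustment for every secondary outcome and so covers feature families for which unadjusted P values are a poor guide, in a trial that makes the microbiome part of its objective. The size is about 5 expected false positives per 100 null features, per contrast and visit (2.5 to 15 for 50 to 300).

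This assumes that features are tested singly at 5% and that the assumed counts are realistic; the article settles neither. The expected number needs no assumption about correlation, whereas the chance of at least one false positive depends on it heavily. The multiplier of two visits applies at most to feces, not to immune subsets in blood.

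The missing lead model is mainly a question of which result is reported and contributes little to false positives.

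**What to change.** 1. Limit the no-adjustment rule to the low-dimensional secondary outcomes.
2. For microbial abundances, fecal metabolites and immune-cell subsets, apply Benjamini-Hochberg false-discovery control (5%, for example) within each family and contrast. State whether the two fecal visits count as one family, and label the results exploratory.
3. Where an outcome is measured at both 2 and 4 months, name the baseline-adjusted mixed model with group-by-visit terms as the lead analysis and read the visit-specific contrasts from it. Keep the separate-visit regressions as supportive only. Outcomes with a single follow-up, such as those in blood, stay with the planned regression.

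The cost is a few sentences in the plan, a little more analysis work and fewer nominally significant findings. No new data are needed, and the sample size and primary analysis do not change.

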### Quality Control and Quality Assurance

The SUN study researchers are trained and monitored by an independent academic research organization based in Auckland, New Zealand. The Green Lane Coordinating Centre conducts training and monitoring in accordance with the International Council on Harmonization—Guideline for Good Clinical Practice within the setting of a nutrition intervention trial. The Green Lane Coordinating Centre performs a centralized review of SUN study data (blinded to intervention allocation) and other documents to assess protocol adherence, data accuracy and completeness, source data verification, and review investigator files.

